## Abstract

**Background:**

Type 2 diabetes mellitus (T2DM) is characterized by systemic metabolic abnormalities and the development of micro- and macrovascular complications, resulting in a shortened life expectancy. A recent cardiovascular (CV) safety trial, the EMPA-REG OUTCOME trial, showed that empagliflozin, a sodium glucose cotransporter 2 (SGLT2) inhibitor, markedly reduced CV death and all-cause mortality and hospitalization for heart failure in patients with T2DM and established CV disease (CVD). SGLT2 inhibitors are known to not only decrease plasma glucose levels, but also favorably modulate a wide range of metabolic and hemodynamic disorders related to CV pathways. Although some experimental studies revealed a beneficial effect of SGLT2 inhibitors on atherosclerosis, there is a paucity of clinical data showing that they can slow the progression of atherosclerosis in patients with T2DM. Therefore, the EMBLEM trial was designed to investigate whether empagliflozin treatment can improve endothelial function, which plays a pivotal role in the pathogenesis of atherosclerosis, in patients with T2DM and established CVD.

**Methods:**

The EMBLEM trial is an ongoing, prospective, multicenter, placebo-controlled double-blind randomized, investigator-initiated clinical trial in Japan. A total of 110 participants with T2DM (HbA1c range 6.0–10.0%) and with established CVD will be randomized (1:1) to receive either empagliflozin 10 mg once daily or a placebo. The primary endpoint of the trial is change in the reactive hyperemia (RH)-peripheral arterial tonometry-derived RH index at 24 weeks from baseline. For comparison of treatment effects between the treatment groups, the baseline-adjusted means and their 95% confidence intervals will be estimated by analysis of covariance adjusted for the following allocation factors: HbA1c (<7.0 or ≥7.0%), age (<65 or ≥65 years), systolic blood pressure (<140 or ≥140 mmHg), and current smoking status (nonsmoker or smoker). Key secondary endpoints include the change from baseline for other vascular-related markers such as arterial stiffness, sympathetic nervous activity, and parameters of cardiac and renal function. Importantly, serious adverse effects independently on the causal relationship to the trial drugs and protocol will be also evaluated throughout the trial period.

**Discussion:**

EMBLEM is the first trial to assess the effect of empagliflozin on endothelial function in patients with T2DM and established CVD. Additionally, mechanisms associating empagliflozin-mediated actions with endothelial function and other CV markers will be evaluated. Thus, the trial is designed to elucidate potential mechanisms by which empagliflozin protects CV systems and improves CV outcomes.

*Trial registration* Unique Trial Number, UMIN000024502 (https://upload.umin.ac.jp/cgi-open-bin/ctr_e/ctr_view.cgi?recptno=R000028197)

**Electronic supplementary material:**

The online version of this article (doi:10.1186/s12933-017-0532-8) contains supplementary material, which is available to authorized users.

## Background

Type 2 diabetes mellitus (T2DM) is characterized by systemic insulin resistance, impaired glycemic homeostasis, increased risk of atherosclerosis, and subsequent cardiovascular (CV) complications [1–3]. The risk of CV disease (CVD) is approximately two to fourfold higher in patients with T2DM than in those without the disease [4, 5]. However, whether glucose-lowering therapy can reduce the CVD risk is controversial [6–8]. The potential effects of agents used to treat T2DM on the CV systems are likely to be independent of their glucose-lowering effect, and they may differ from agent to agent. Therefore, it is vitally important to elucidate the actions, outcomes, and safety of such agents on the CV system. This will enable physicians to appropriately tailor each individual’s glucose-lowering medication to reduce their risk for CV complications and adverse outcomes.

Recent CV safety trials with newer glucose-lowering agents have raised important clinical implications and several research questions [9]. Among them, the EMPA-REG OUTCOME trial—in which the long-term CV safety of empagliflozin was investigated—initially exhibited superior CV benefits relative to placebo treatment in patients with T2DM and established CVD, but later no significant risk reduction in vascular events was noted [10]. Empagliflozin is one of the sodium–glucose cotransporter 2 (SGLT2) inhibitors that work in the proximal renal tubules by diminishing the reabsorption of glucose from the glomerular filtrate back into the circulation. This results in increased urinary glucose excretion and decreased plasma glucose concentrations independent of insulin secretion and insulin action [11, 12]. Although the mechanisms by which empagliflozin could reduce hospitalization for heart failure and mortality remain unclear, several reports have proposed that SGLT2 inhibitors could modulate favorably a wide range of metabolic, neurohormonal, and hemodynamic pathways related to CVD [13–17]. Given the favorable nature of the mechanisms of action of SGLT2 inhibitors which are indeed multifactorial, it is highly conceivable that SGLT2 inhibitors can potentially attenuate atherogenesis and reduce subsequent CV event risks such as myocardial infarction and stroke, despite the vascular event risk profile identified in the EMPA-REG OUTCOME trial [10]. The potential of SGLT2 inhibitors to ameliorate atherosclerosis risk in the clinical setting in the short- and long-term remains to be elucidated.

Impaired endothelial function plays the pivotal role in the pathophysiology of atherogenesis and is usually accompanied by increased oxidative stress and inflammatory responses [18]. In addition to atherosclerosis, impaired endothelial function is associated with various type of CVD, including heart failure [19–22]. Moreover, elevated markers indicative of endothelial dysfunction are closely associated with T2DM [23, 24]. Reactive hyperemia-peripheral arterial tonometry (RH-PAT) is a noninvasive and reproducible examination technique for assessing peripheral microvessel endothelial function [25, 26]. A growing body of evidence suggested that RH-PAT-proven endothelial dysfunction can predict future CV events [27–29], and some drug-intervention studies successfully demonstrated improvements in the endothelial function of patients with T2DM [30–32]. Thus, it seems reasonable to evaluate the beneficial effects of SGLT2 inhibitors on atherosclerosis based on the surrogate marker of endothelial function.

Founded on this rationale, the EMBLEM trial was designed to evaluate the effect of empagliflozin on endothelial function—as assessed by RH-PAT—in patients with T2DM and established CVD. This trial presents an opportunity to further investigate the effects of empagliflozin and to gain a better understanding of the possible mechanisms by which it contributes to mediating endothelial function to elicit beneficial CV effects.

## Methods

### Trial overview and design

The EMBLEM trial is an ongoing, prospective, multicenter, placebo-controlled double-blind randomized, investigator-initiated clinical trial. The trial was designed to test the hypothesis that empagliflozin can improve endothelial function in patients with T2DM and established CVD compared with a placebo. Patients will be recruited and randomized in blinded manner to either empagliflozin or placebo treatment group. Following 24 weeks of treatment, the effects of empagliflozin on endothelial function in comparison to placebo will be evaluated using the RH-PAT index (RHI).

The local institutional review boards and independent ethics committees approved the trial protocol. The trial is to be conducted in full compliance with the articles of the Declaration of Helsinki and according to the Ethical Guidelines for Medical and Health Research Involving Human Subjects established by the Ministry of Health, Labour, and Welfare and the Ministry of Education, Culture, Sports, Science, and Technology in Japan. The EMBLEM trial was registered by the UMIN in October 2016 (ID: 000024502). The trial drugs were purchased from Boehringer Ingelheim.

### Trial population and recruitment

We aim to recruit a total of 110 participants across approximately 17 sites in Japan. Recruitment for the trial began in January, 2017, and will end in October, 2017. Eligible participants for the trial are patients aged ≥20 years with T2DM who meet the enrollment criteria detailed in Table 1. Briefly, eligible patients include those with a diagnosis of T2DM, a HbA1c ranging from 6.0 to 10.0%, on stable glucose-lowering agents for at least 1 month before providing consent, and a previous history of CVD, that includes chronic heart failure (CHF), coronary artery disease (CAD), stroke, occlusive peripheral artery disease, or the presence of coronary artery stenosis (≥50%) as detected by angiography or multi-slice computed tomography. CHF must range from classification I to III in accordance with the New York Heart Association (NYHA) functional classification system. In addition, the NYHA classification and medical treatment for CHF (including angiotensin-converting enzyme inhibitors, angiotensin II receptor blockers, beta-blockers, and diuretics) must remain unchanged for 1 month before consent to participate is provided. Cardiac systolic functions may be reduced or preserved. After initially screening for eligibility using prior medical records, each patient will receive an adequate explanation of the trial plan before they provide written informed consent.

**Table 1 Tab1:** Comprehensive inclusion and exclusion criteria

Inclusion	Exclusion
Adults (aged ≥20 years)	Type 1 diabetes mellitus
T2DM with HbA1c ≥6.0% and <10.0%, unchanged dosage of glucose-lowering agent(s) within 1 month before consent is provided, investigator considers the patient can start or add/switch to the trial drug	History of diabetic ketoacidosis or diabetic coma within the last 6 months
	Severe renal dysfunction (eGFR < 45 mL/min/1.73 m^2^ or undergoing dialysis)
Patients with at least one of the following conditions:	Serious liver dysfunction (AST or ALT is 3 times higher than site reference value)
CHF (NYHA classification I–III, systolic or diastolic failure) not changed NYHA classification and receiving unchanged heart failure medication within 1 month before consent is provided	
	CHF (NYHA classification IV)
	Hypotension (systolic blood pressure <90 mmHg)
	Pituitary gland dysfunction or adrenal gland dysfunction
History of CAD (myocardial infarction and angina) or cerebral infarction	History of CAD, cerebrovascular disease, or TIA within 3 months before consent
Previous coronary revascularization (PCI and CABG)	History of coronary revascularization (PCI and CABG) within 3 months before consent
Presence of coronary artery stenosis ≥50% luminal narrowing depicted by angiography or MSCT	
	Patients received SGLT2 inhibitor within 1 month before consent
Diagnosis of arteriosclerosis obliterans	
Patients who received an explanation of the study and provided written informed consent	Pregnant or suspected pregnancy
	Lactating
	History of hypersensitivity to ingredients of empagliflozin
	Considered inappropriate for the study by investigators due to other reasons, such as malignant complications

*ALT* alanine aminotransferase, *AST* aspartate aminotransferase, *CABG* coronary artery bypass grafting, *CAD* coronary artery disease, *CHF* chronic heart failure, *eGFR* estimated glomerular filtration rate, *MSCT* multi-slice computed tomography, *NYHA* New York Heart Association, *PCI* percutaneous coronary intervention, *SGLT2* sodium glucose cotransporter 2, *TIA* transient ischemic attack, *T2DM* type 2 diabetes mellitus

### Trial design and follow up

All consenting and eligible participants are randomized to receive either empagliflozin or a placebo treatment. Post-randomization follow-up visits are scheduled at 4, 12, and 24 weeks (Fig. 1). Each participant will see their usual-care physician at each visit to receive usual-care and individualized treatment according to their background disease, in addition to administration of the study drug.

**Fig. 1 Fig1:**
[figure not shown]
Trial design

### Randomization and blinding

Eligible and consenting participants will be randomized (1:1), in a double-blind manner to either receive empagliflozin (10 mg once daily) or a placebo treatment (once daily), using the web-based minimization dynamic allocation method balancing for HbA1c (<7.0 or ≥7.0%), age (<65 or ≥65 years), systolic blood pressure (BP) (<140 or ≥140 mmHg), and current smoking status (nonsmoker or smoker) at the time of screening [33, 34].

After randomization, patients, investigators, the sponsors, and other individuals involved with various aspects of the trial (e.g., including the conduct or data analysis) are to remain masked to group assignments until after the database is locked and prior to the statistical analysis. Only a predesignated study person will have access to the sealed randomization key codes that will allow unblinding under circumstances considered an emergency and when the identity of the trial drug must be revealed strictly to the investigator for the purpose of providing appropriate medical treatment due to serious adverse effects or ensuring the safety of a trial participant. If the key code for any patient is opened, the principal investigator must be informed immediately of the unblinding incident.

### Treatment

All participants will be followed-up for 24 weeks. Although no specific glycemic target was set (e.g., HbA1c) in the present trial, all participants are to be treated in accordance with the treatment guidelines for T2DM and the official recommendations for appropriate use of SGLT2 inhibitors from the Japan Diabetes Society [35, 36]. Each participant’s pretrial or background glucose-lowering therapy is to remain unchanged during the trial if their medical condition is not compromised by such an approach. However, if participants in either treatment group cannot achieve their glycemic goal, the coadministration of glucose-lowering agents other than SGLT2 inhibitors, or increased dosages of the other glucose-lowering agents will be allowed, if the risk of developing hypoglycemia is minimized. If a patient’s blood glucose exceeds 13.3 mmol/L (>240 mg/dL) after an overnight fast, confirmed by a second measurement on different day, rescue medication can be initiated for the treatment of hyperglycemia. The initiation, choice, and dosage of rescue medication(s) are at the investigator’s discretion. Rescue medication can include an up-titration of a background treatment. If insulin is a background therapy, changes of >10% of the total daily prescribed-dose of insulin are considered rescue therapy. All rescue medication is to be taken in accordance with the prescribing information, with consideration given to minimizing the potential for contraindications and the risk for hypoglycemia. After the trial is completed, all participants can select any glucose-lowering treatments in accordance with their individual requirements.

### Measurements

The baseline characteristics of all patients, including gender, age, body height, body weight (BW), duration of T2DM, complications, background treatment, and smoking and drinking habits are to be recorded prior to randomization. Each participant’s background treatment and trial medication will be recorded at each visit. BP, heart rate (HR), and BW will be measured at baseline and at each visit. The following assessments and methodology will be employed at baseline and at 24 weeks: peripheral endothelial function will be assessed using the RH-PAT test (details described later), the R–R interval coefficient of variation will be determined using electrocardiograms, left ventricular ejection fraction (LVEF) using the modified Simpson method and E/e’ using the tissue Doppler imaging will be measured by echocardiograms, brachial–ankle pulse-wave velocity (baPWV) will be measured using a volume-plethysmographic apparatus as previously described [37]. These physiological tests are to be evaluated locally by technicians at each site. Blood tests will also be performed at baseline and 24 weeks (details listed in Additional file 1), as will specific biomarker assays for N-terminal pro-brain natriuretic peptide (NT-proBNP), interleukin-8 (IL-8), high-sensitivity troponin-I (hs-TnI), receptors for advanced glycation end products (RAGE), and angiopoietin-like protein 2 (ANGPTL2). Biomarkers will be measured at central laboratories. Urinary ketone bodies are to be evaluated qualitatively at each visit. Creatinine-corrected urinary albumin excretion and urinary liver-type fatty acid-binding protein (L-FABP) will be measured at baseline and 24 weeks. In addition, participants will be examined at each visit for symptomatic genital or urinary infections that need to be treated with antibiotics.

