### Safety

Throughout the study, safety will be reported for the intention-to-treat population by recording the serious adverse events (AEs) regardless of causal relationship to the trial drugs and protocol, and pre-defined adverse events of special interest (AESI) such as hepatic injury, decreased renal function, metabolic acidosis, ketoacidosis, diabetic ketoacidosis, and events involving lower limb amputation (details in Additional file 2). When the investigators confirm these AEs, their severity or grade, procedures conducted, outcomes, and relationship to the study drug will be assessed. Investigators will promptly report the incidence of AEs to the secretariat who will in turn promptly report to the principal investigator. The principal investigator must report expeditiously to Nippon Boehringer Ingelheim and the Data and Safety Monitoring Board (DSMB). The DSMB consists of an authorized endocrinologist and clinical epidemiologists with relevant expertise. Blinded to treatment allocation, the DSMB will independently evaluate safety during the trial and also assess the necessity for any revisions to the trial design and validate any decisions to continue the trial. If needed, the DSMB will make recommendations on safety issues to the principal investigator. Criteria governing withdrawal from the trial are listed in Table 2.

**Table 2 Tab2:** Discontinuation criteria

Severe hypoglycemia
Seriously poor glycemic control (HbA1c ≥10.0%)
Development of diabetic ketoacidosis
Serious dehydration requiring rehydration therapy
Considered inappropriate to continue the trial by investigators due to aggravation of primary disease or complications
Considered inappropriate to continue the trial by investigators due to adverse side effects of the trial drug
Considered inappropriate to continue the trial by investigators due to some other reasons
Participant withdrawal of consent

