This trial has several limitations. First, it includes a relatively small sample size. Second, although the RH-PAT test is noninvasive, easy to perform, and an operator-independent method, its measurement is prone to be affected by individual physical conditions, intravascular volume, and the examination room environment. To minimize any such influences at participating institutions, investigators must perform the test in accordance with the EMBLEM-style operation manual which is modified from the manufacturer’s instruction (Additional file 4). In addition, because the empirical prediction implies that changes in the RHI in response to treatment may differ according to the RHI level, we plan to analyze data using subgroups stratified by the RHI level at baseline, as a subgroup analysis. Finally, SGLT2 inhibitors can potentially trigger some characteristic adverse drug reactions, such as intravascular volume depletion and urinary tract and genital infections, especially in the elderly and women [79]. Hence, investigators are cautioned to monitor patients for such reactions throughout the trial. In addition, information will be collected on predefined AESI as described earlier.

In summary, with the recent accumulation of evidence suggesting that SGLT2 inhibitors have CV and renal protective effects beyond glucose-lowering, the clinical use of SGLT2 inhibitors in patients with T2DM and established CVD could gain increased momentum.

Therefore, further assessments of the mechanisms that underpin the functionality of SGLT2 inhibitors are certainly warranted. The EMBLEM trial is the first study to assess the effect of empagliflozin on endothelial function in patients with T2DM and established CVD. In addition, possible mechanisms driving empagliflozin-mediated interactions between endothelial function and other CV markers will be evaluated. This trial has the potential to reveal profound mechanisms of action by which empagliflozin protects the CV system and improves CV outcomes in the EMPA-REG OUTCOME trial.

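### The visit check for genital and urinary infections is limited to those needing antibiotics, narrower than the drug reaction the protocol asks investigators to monitor, so milder cases may go unrecorded

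*Protocol article*

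**What the plan says.** Three parts of the protocol article bear on this point.

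- **Measurements.** The visit check reads: "participants will be examined at each visit for symptomatic genital or urinary infections that need to be treated with antibiotics". It sets two conditions, symptoms and a need for antibiotics. On timing, Trial design and follow up states: "Post-randomization follow-up visits are scheduled at 4, 12, and 24 weeks".
- **Discussion, limitations paragraph.** Characteristic adverse reactions to SGLT2 inhibitors are described, "such as intravascular volume depletion and urinary tract and genital infections, especially in the elderly and women". No severity or treatment condition is attached. The text continues: "Hence, investigators are cautioned to monitor patients for such reactions throughout the trial". It then presents the collection of predefined adverse events of special interest (AESI) as a further item.
- **Safety.** Safety is reported by "recording the serious adverse events (AEs) regardless of causal relationship to the trial drugs and protocol", together with predefined AESI. The AESI named as examples are "hepatic injury, decreased renal function, metabolic acidosis, ketoacidosis, diabetic ketoacidosis, and events involving lower limb amputation (details in Additional file 2"). Genital and urinary infections are not among them. The list is not exhaustive, and the additional file is not shown.

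**The concern.** The reaction that investigators are told to watch for is wider than the event that the visit examination looks for. The difference between the two is a treatment condition, which is not a feature of the infection itself. Two patients with the same symptoms can fall on opposite sides of the line because one was judged to need an antibiotic and the other was not, or was managed in another way.

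If the visit check is followed as worded, a non-serious symptomatic infection managed without antibiotics is not looked for there. It is also not visibly recorded under Safety. At stake is how completely the trial describes a reaction that the protocol itself regards as characteristic of the drug. With 55 patients per arm, few events can be expected in any case, so losing some of them could leave a table that reflects the recording rule more than the drug.

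**Working it through.** **Step 1: follow each type of infection through the text.**

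| Infection | Visit check (Measurements) | Safety section | Monitoring caution (Discussion) |
|---|---|---|---|
| Serious, any treatment | Yes, if symptomatic and needing antibiotics | Yes, as a serious event | Yes |
| Non-serious, symptomatic, needs antibiotics | Yes | Not visibly | Yes |
| Non-serious, symptomatic, managed without antibiotics | No | Not visibly | Yes, but no recording rule is given |

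The third row is the gap. The only statement covering it is the caution in the limitations paragraph, which asks for monitoring but does not say what is written down.

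**Step 2: what the filter does to the numbers.** The documents give no infection risk and no share needing antibiotics, so there is no figure in the plan to reproduce. The following is an illustration with assumed values.

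Inputs:
- n = 55 per arm (Sample size estimation).
- True risks p_A (empagliflozin) and p_P (placebo): assumed.
- Share s of affected patients who meet the antibiotic condition: assumed, and the same in both arms.

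Formulas:
- expected counted cases on empagliflozin = 55 × p_A × s
- counted difference = (p_A − p_P) × s
- chance of no counted case on empagliflozin = (1 − p_A × s)^55

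| p_A, p_P | s | Expected cases, empagliflozin | Counted difference (points) | Chance of no case, empagliflozin |
|---|---|---|---|---|
| 4%, 1% | 1 | 2.2 | 3.0 | 11% |
| | 0.5 | 1.1 | 1.5 | 33% |
| | 0.25 | 0.55 | 0.75 | 58% |
| 8%, 3% | 1 | 4.4 | 5.0 | 1% |
| | 0.5 | 2.2 | 2.5 | 11% |
| | 0.25 | 1.1 | 1.25 | 33% |
| 12%, 5% | 1 | 6.6 | 7.0 | 0.1% |
| | 0.5 | 3.3 | 3.5 | 3% |
| | 0.25 | 1.65 | 1.75 | 19% |

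For the middle case with s = 0.5: 55 × 0.08 × 0.5 = 2.2; (0.08 − 0.03) × 0.5 = 0.025; (1 − 0.04)^55 = 0.106.

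**Step 3: the relative comparison.** With the same s in both arms, the risk ratio is (p_A × s)/(p_P × s) = p_A/p_P, so s cancels. At 8% and 3% it is 2.67 for every s. It moves only if s differs by arm. With s = 0.5 on empagliflozin and 0.75 on placebo it becomes 0.04/0.0225 = 1.78; with the shares reversed it becomes 0.06/0.015 = 4.0. The documents give no reason to expect either.

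**The case against.** The strongest case against has five parts.

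- **General monitoring is already requested.** The Discussion asks investigators to watch for these reactions without an antibiotic condition. This stands, so it would be wrong to say that infections are sought only when antibiotics are needed. It does not close the gap, because a caution in a limitations paragraph sets no recording rule.
- **Recording may be fixed elsewhere.** The AESI list is given by example, Additional file 2 is not shown, and an article commonly leaves case report forms to the full protocol. This also stands, so a reader cannot conclude that no route exists. Two things still favour the concern: the narrower condition is stated in the article, not merely left out, and the Discussion treats AESI collection as additional to monitoring for these reactions.
- **The sentence describes an examination, not a counting rule, and refers to need, which is a clinical judgement.** This is fair. Nothing shows that sites will count by prescriptions issued. The condition still turns on treatment, and no other visit-by-visit rule is visible.
- **The filter is the same in both double-blind arms.** This is correct and limits the claim. A reader might infer that the comparison is biased in favour of empagliflozin because more cases would be missed there. More cases would be missed there only if more occur there. With an equal share the ratio is preserved, and only the absolute difference shrinks.
- **No planned test depends on it.** Infections are not among the listed endpoints, the analysis section names no infection comparison, and the sample size rests on the RH-PAT index. This stands and keeps the point minor.

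**Conclusion.** The point holds as a mismatch between two stated rules. The visit examination covers symptomatic infections needing antibiotics; the reaction to be monitored is urinary tract and genital infection in general. Non-serious symptomatic infections managed without antibiotics may therefore go unrecorded.

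If they do, counts fall in both arms and the absolute difference shrinks in proportion to the share needing antibiotics. How far cannot be derived from the documents. In the illustration, the difference is halved or quartered when half or a quarter of the cases qualify, and nothing is lost when all do. Those figures rest on assumed risks, an equal share in both arms, all 55 patients per arm observed, and independent patients with at most one counted case each.

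A reader might go further and infer that an undercount is certain. The documents do not support this: they give neither a rate nor a share, and part of the safety material is not shown. The primary endpoint, its analysis and the sample size are unaffected.

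**What to change.** Reconcile Measurements with the Discussion. At the visits already scheduled, record every symptomatic genital or urinary infection, whatever its treatment, and enter the treatment given (none, antibiotic, other) as a separate field. Report by arm both the total and the antibiotic-treated subset, so that the category now described in the article remains available. If the full protocol or Additional file 2 already does this, aligning the sentence in Measurements is enough.

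The cost is a wording change, one extra field and a few more mild events to record; no visit is added. The change concerns data capture only and says nothing about how infections should be treated.
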